### ***DSMB Meetings***

Precluding an occurrence of adverse events at previously described percentage or an SAE, the DSMB will meet via phone conference at the start of the project, and at Day 31 of the trial. Additional DSMB teleconferences will be scheduled as the Chair recommends. The agenda will be prepared by the DSMB Chair in consultation with the study investigators.

At least five business days before the DSMB the Principal Investigator will send study materials to the DSMB members to allow time to review the material before the meeting. The Principal Investigator and team will be responsible for the preparation of meeting materials and all DSMB meeting arrangements.

Closed sessions of the DSMB will be attended only by the voting DSMC members, the Executive committee, and the study statisticians. The closed session may be called when the DSMC reviews the safety and impact data unmasked as to random assignment. At the discretion of the DSMC Chair, the committee can meet in Executive session with only the five voting members present to discuss issues and take formal votes as needed.

Meeting minutes will be prepared by the Chief Investigator for the trial. Draft minutes will be combined and distributed to the Chair for review and changes before distribution to the entire committee and study team members. The minutes shall summarize all recommendations.

DSMB members must make every effort to attend DSMB meetings. If a member fails to make a meeting, it should be ensured that the member makes the next meeting. If a member fails to make the second meeting, the member will be replaced.

All data presented to the DSMB is considered confidential, and cannot be revealed to those outside the study until after publication.

### ***Protocol Changes and Ancillary Studies***

The DSMB will be informed of any major study protocol changes, and DSMC concurrence will be sought on substantive recommendations for changes prior to their implementation. Ancillary studies affecting the trial will be brought forward to the DSMC for their information. The DSMC will review them for possible impact on the main trials. The DSMC will not make recommendations regarding whether the studies may or may not proceed, which is the province of the Executive committee.

### ***Recommendations***

DSMB recommendations will be provided to the study leadership. If the recommendations involve participant safety, the Principal Investigator, in collaboration with the site investigators, will act to implement the change as expeditiously as possible. However, if the study leadership does not concur with the DSMB recommendations, it will be the responsibility of the study leadership and DSMB Chair to reach a mutually acceptable decision for implementation, and a report issued to the DSMB.

### **I. Sociodemographic characteristics**

- a. Age \_\_\_\_|\_\_\_\_|\_\_\_\_ Years
- b. Sex (underline)    Male    Female
- c. Marital status (underline) Single, Married, Widowed, Divorced
- d. Education (underline)
- e. Occupation (social responsibility)

### **II. Awareness of drug distribution**

1. Has there been any mass drug distribution in this community recently? (Probe further on how long ago was this done? What was the purpose of the drug?)
2. How did you get to know about the distribution exercise (probe further on adequacy of information provided and the person who did the distribution)

### **III. Process of drug distribution**

3. How was the distribution done? (Probe for Pre distribution exercises, time of the day and feasibility Strategy used and feasibility)
4. In your opinion did everyone in the community receive the drugs? (probe further on category of people who received the drug and those exempted)

### **IV. Opinion about drug distribution**

5. Which arm of the distribution was your community (triple co-administration or the standard MDA)
6. Were you satisfied with the present way of drug distribution? (probe further how the current MDA approach differed from previous or current standard MDA)
7. What suggestions do you have for improving future distribution exercises (probe further pill number (burden), strategy, timing, distributors)

### **V. Community factors**

8. What is the community/your perceptions towards the types of MDA, triple-co administration vs standard (probe further on number of complaints, logistical, socio-cultural, religious factors).

### **VI. MDA related Factors**

9. What are the triple co-administration related challenges? How do community, family and/or close associate relate any complaint to the approach? (probe further on the nature of the complaints, duration and number)

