#### 5.1.2. **Secondary Objective:**

- Understanding the perceptions of the beneficiaries receiving the co-administration of azithromycin, ivermectin, and albendazole especially surrounding pill burden and the change in MDA distribution schedule.
- Understanding the perceptions of the co-administration strategy by the local health workforce as a means of PC-NTD drug delivery.
- A cost analysis comparing existing MDA unit costs from woredas within the region already on a standard MDA schedule with that of the co-administered woredas.
- A literature/data review across 19 different countries including Ethiopia which will analyse the possible benefits of co-administration from an economic and epidemiological standpoint when compared with current trends towards achieving 2020 NTD control and elimination goals.

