**Study Goal:** Triple drug administration may present an opportunity to significantly lessen the time investment required for beneficiaries to participate in all of the necessary mass drug administrations, time that could otherwise be used for farming, time at the market, etc. Lessening the time a beneficiary needs to invest to receive drug administration may subsequently improve MDA coverage.

This sub-study will seek to discover, through a series of in-depth interviews and focus groups within the trial arm the benefits and disadvantages of the co-administration strategy.

**Study area:** The study will take place within the same goles selected for the trial arm

**Study Sample:** The target participants will be selected among the beneficiaries living within the goles where the co-Administration of azithromycin, ivermectin and albendazole took place. In order to ensure that experience is not influenced by possible logistic or programmatic challenges unique to a given area, selection of participants will be randomized using the RANDNUM function from a total list of the 8000 participants derived from the pre-MDA census. This process will be continued (excluding any beneficiaries already chosen) until a total of 100 interviewees have been selected.

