**Patient Interview Structure:** Patients will be interviewed within the community by an Amharic-speaking interviewer as well as an interpreter fluent in the mother tongue of the area. It is important to note that Affan Oromo is the *lingua franca* for Oromia. The patient interviews will take place within the interviewee's home or in a private area surrounding the distribution point, and in an environment which is secluded from members of the surrounding community in order to discourage peer and community influence on the interviewee. The interviews will take place either immediately after the beneficiary receives his/her co-administered dose or during the post-MDA active follow-up that will take place the following day. Written consent will be obtained from all participants using the form in **Appendix 9**. While the interview structure will seek to move beyond yes/no questions and foster real discussion, basic topics will include: 1.) A description of the recipient's "average day" in terms of work, child-rearing, etc. 2.) A description of what the recipient believes are the biggest health issues within the community, 3.) The recipient's thoughts on the role of the HEW, 4.) Perceptions surrounding the "usual" MDA distribution and how it affects the "average day" of the recipient, 5.) Perceptions of "usual" MDA versus the co-administration, 5.) Perceptions of pill burden, both for the recipient and the recipient's family. Interviewers will be trained in the reduction of biases when conducting these interviews.

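### The appended interview guide prompts for challenges and complaints of the triple regimen but not for benefits or time saved, and reaches pill burden only as a probe, so it fits the sub-study's two-sided goal poorly

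*Protocol*

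**What the plan says.** Section 5.1.2 makes beneficiaries' perceptions a secondary objective, "especially surrounding pill burden and the change in MDA distribution schedule". The outcome list in Section 10 repeats this. Section 11, item I, sets the sub-study the task of finding "the benefits and disadvantages of the co-administration strategy" and gives less time lost to drug distribution as the expected gain. Its interview structure lists six topics, one of which is "Perceptions of pill burden, both for the recipient" and the recipient's family.

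The guide at the end of the appendices has nine items:

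- Items 1 to 4 cover awareness and process, and item 5 asks the arm.
- Item 6 asks about satisfaction and how the approach differed from standard MDA.
- Item 7 asks for suggestions, with the instruction "probe further pill number (burden), strategy, timing, distributors".
- Item 8 asks "What is the community/your perceptions towards the types of MDA, triple-co administration vs standard", with the instruction "probe further on number of complaints, logistical, socio-cultural, religious factors".
- Item 9 asks "What are the triple co-administration related challenges", with the instruction "probe further on the nature of the complaints, duration and number".

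**The concern.** A goal that covers both benefits and disadvantages needs prompts for both. This guide asks outright for the difficulties of one regimen. It asks neither for that regimen's advantages nor for the difficulties of the comparator. Section 11 says the analysis will code what participants say, so a subject the interviewer does not raise may leave little to code.

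Two subjects are exposed. The first is time saved, the expected benefit, which no item or probe names. The second is pill burden, the named focus, which is raised only when the respondent has been asked what to improve. Section 11 itself says that any distress from taking up to nine pills has to be established before a national programme adopts the strategy. Statements gathered only as suggestions are a weak basis for that.

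**Working it through.** There is no figure to reproduce. The check sets the nine guide items against the stated outcome and goal.

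**Step 1. What each opinion item asks.**

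| Item | Main question | Probes |
|---|---|---|
| 6 | Satisfaction; either direction, though worded as yes/no | Difference from standard MDA; neutral |
| 7 | Suggestions for improvement | Pill number, strategy, timing, distributors |
| 8 | Perceptions of triple versus standard; open and neutral | Number of complaints first; then logistical, socio-cultural and religious factors |
| 9 | Challenges of the triple regimen only | Nature, duration and number of complaints |

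**Step 2. Counts over the nine items.**

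- Main question confined to challenges: 1 of 9 (item 9).
- Complaints named in a probe: 2 of 9 (items 8 and 9).
- Benefits, advantages or time saved named in a question or probe: 0 of 9.
- Challenges of standard MDA asked in the same terms as item 9: 0 of 9.
- Pill burden named: 1 of 9 (item 7, as a probe). The family's pill burden: 0 of 9.
- Open or neutral opinion questions that can draw a favourable answer: 2 of 9 (items 6 and 8).

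**Step 3. Comparison with the goal and outcome.** The disadvantage side of the goal has an explicit question. The benefit side depends on what respondents volunteer under items 6 and 8. Of the two named focuses, the schedule change is reachable through the comparisons in items 6 and 8 and the timing probe in item 7. Pill burden is reachable only through the item 7 probe.

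**Step 4. Comparison with Section 11's six topics, conditional on this being the beneficiary guide.** One topic, usual MDA versus co-administration, is asked directly (items 6 and 8). One, pill burden, is a probe only. Four have no question of their own: the average day, the main health issues, the HEW's role, and how usual MDA affects the day. That gives 1 + 1 + 4 = 6. The last of the four is partly touched, since items 6 and 8 invite comparison with standard MDA. This tally depends on the condition; the counts in step 2 do not.

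**The case against.** The strongest objection is that the guide may not be the instrument described in Section 11. Its heading and intended respondents are not in the available text. Section 11 places the sub-study in trial-arm communities and interviews people right after the dose or the next day. The guide asks which arm the community was in and how long ago a distribution took place. It also asks whether everyone in the community received drugs, which could suit a community informant or a group. Section 11 provides for both interviews and focus groups, so there may be more than one instrument. This stands, and it is why the six-topic tally is only conditional. It does not rescue item 9, whose wording is lopsided whoever answers it.

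A second objection is that the guide is semi-structured, that Section 11 fixes the missing topics as interview content, and that interviewers will be trained to reduce bias. This also stands in part. But if this is the beneficiary guide, the protocol then gives two differing specifications for the same interviews, and training does not add questions that the printed guide lacks.

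A third is that items 6 and 8 are neutral and item 7 is put to every respondent, so its pill-burden probe is not limited to a selected subgroup. That is correct. It limits the conclusion to unequal prompting. It does not make an open question equivalent to an explicit request for challenges.

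**Conclusion.** The point holds in a limited form. The guide is not aligned with the sub-study's two-sided goal or with its named focus on pill burden. It collects the perceptions outcome incompletely, with prompts weighted towards negatives. This rests on the guide being used as printed.

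A reader might infer more, and the documents do not support it:

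- **That the guide fails to collect the acceptance outcome.** Items 6 to 8 collect part of it.
- **That the result will be a one-sided list of problems.** Favourable answers are possible under items 6 and 8. A tilt is plausible but not shown.
- **That the time-saving hypothesis will have no data.** Section 11 lists the effect of usual MDA on the recipient's day as a topic, and items 6 to 8 can draw remarks on time.
- **That four of six required topics are missing.** This presumes a role for the guide that cannot be confirmed.
- **That the primary result is at risk.** Section 5.1.1 includes acceptance in the primary objective, but Section 10 makes the primary outcome the incidence of AEs/SAEs and lists perceptions as secondary. The safety comparison, margin and sample size are untouched.

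This is a small, inexpensive improvement to a qualitative secondary outcome.

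**What to change.** Before interviewer training:

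1. Replace item 9 with a balanced pair: what was better or easier, and what was worse or harder, about receiving all three drugs together. Ask the same pair, in the same words, about the standard two-round MDA.
2. Add one direct open question on the number of tablets, for the respondent and for the family.
3. Add one open question on time spent or work missed under each schedule.
4. State on the guide which respondents and which arm it is for. If it is the beneficiary guide, bring it into line with the topics in Section 11.

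The cost is about a page of rewording and a slightly longer interview.
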